### Outcomes

#### Effect Measures

The effect of the intervention will be assessed at the individual level for both family caregivers and people living with schizophrenia.

For family caregivers, the outcomes will include knowledge and skills about caregiving (Knowledge and Skill of Caregiving for Schizophrenia, self-developed), social support (Multidimensional Scale of Perceived Social Support) [50], coping (Simplified Coping Style Questionnaire) [51], perceived stigma (Perceived Devaluation and Discrimination Scale) [52], caregiver burden (Zarit Burden Interview [ZBI]) [53], family functioning (Family Adaptation, Partnership, Growth, Affection and Resolve Index scale) [54,55], positive feelings (Caregiving Rewarding Feelings) [56], perceived stress (Perceived Stress Scale) [57], depression (Patient Health Questionnaire-9 [PHQ-9]) [58], and anxiety (Generalized Anxiety Disorder Scale-7 [GAD-7]) [59].

For people living with schizophrenia, the outcomes will include clinical symptoms (Brief Psychiatric Rating Scale [BPRS]) [60] and overall functioning (Global Assessment of Functioning [GAF]) [61], which will both be rated by psychiatrists. Other outcomes will include self-reported quality of life (World Health Organization Quality of Life Brief Scale) [62], recovery (Recovery Assessment Scale [RAS]) [63], rehospitalization, depression (PHQ-9) [58], and anxiety (GAD-7) [59].

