#### Cost Measures

Costs will be measured from a societal perspective and consist of at least the following three levels: (1) costs of the intervention, (2) health care utilization costs, and (3) costs associated with lost productivity. All of the costs will be converted to that for the year 2019 using consumer price indices.

The intervention costs pertain to implementation and operation of the WIFI program. A bottom-up approach will be used to assess the intervention costs, which may include but are not limited to (1) training of psychiatrists, researchers, and other project team members and (2) the WeChat intervention (WOA fee, administrator time, consultation fee of the psychiatrists, etc).

The health care utilization costs pertain to medical care for both people living with schizophrenia and family caregivers. A monthly cost diary will be used to retrospectively track medical expenses incurred by people living with schizophrenia and family caregivers, which may include but are not limited to (1) visits to health care professionals in primary or secondary care; (2) hospitalization; (3) visits to alternative medicine therapists; (4) medication; and (5) other nonmedical expenses associated with medical care, such as transportation, food, and lodging. Health care utilization costs will be estimated by China guideline prices that are supplemented by population-based estimates in the literature.

The costs associated with productivity loss will be assessed at both the people living with schizophrenia and caregiver levels. For both people living with schizophrenia and caregivers, costs include absenteeism due to sick leave, which will be assessed by monthly sick leave calendars. The human capital approach will be used to calculate the costs of losses to production due to sickness or caregiving (net number of days on leave during follow-up multiplied by the daily wage of the worker if employed or an equivalent value if unemployed).

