### Data Collection and Management

Data are collected from people living with schizophrenia, their family members, and psychiatrists at baseline (months 1-2) and at 4, 6, 8, and 10 months. A pilot study with face-to-face interviews was recently completed with 400 families of people living with schizophrenia prior to the formal WIFI program to test all measures and collect baseline data. For this data collection, all participants will be invited through WeChat to complete questionnaires through an online survey known as Sojump [70]. Sojump provides a series of services including questionnaire design and distribution, data collection, and analysis. In addition, all qualitative information (on process measures) will be collected by online one-to-one interviews through WeChat video chat. Each family will be reimbursed with money for participation each time, which will depend on the completion of their relevant questionnaires (about 20 minutes for the people living with schizophrenia and 45 minutes for the caregivers). The reimbursement will increase by 25% for each successive assessment to reflect participants’ ongoing study commitment. Specifically, participants will receive RMB 35 (US $5) for the baseline measurement, followed by RMB 44 (US $6.25), RMB 55 (US $7.81), RMB 69 (US $9.77), and RMB 86 (US $12.21) for the subsequent assessments. A family will be reimbursed with a total of RMB 289 (about US $41) for completion of all five assessments. Payment will be sent directly to one designated family member through the WeChat money transfer function. The double entry method will be adopted to input data, with the range for data values preset to avoid any wrong input. All data will be safely stored on a disk and managed by a special data specialist. Table 3 provides an overview of all outcome measures and assessment instruments that will be used in this trial.

**Table 3 table3:** Assessment of study outcomes.

Outcome measures		Assessment				
		M_1-2_^a^	M_3-4_	M_5-6_	M_7-8_	M_9-10_

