**People living with schizophrenia**						
	Symptoms (Brief Psychiatric Rating Scale)	Yes	Yes	Yes	Yes	Yes
	Functioning (Global Assessment of Functioning)	Yes	Yes	Yes	Yes	Yes
	Quality of life (World Health Organization Quality of Life Brief Scale)	Yes	Yes	Yes	Yes	Yes
	Recovery (Recovery Assessment Scale)	Yes	Yes	Yes	Yes	Yes
	Rehospitalization	Yes	Yes	Yes	Yes	Yes
	Depression (Patient Health Questionnaire-9)	Yes	Yes	Yes	Yes	Yes
	Anxiety (Generalized Anxiety Disorder Scale-7)	Yes	Yes	Yes	Yes	Yes

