### Cost-Effectiveness Analyses

A cost-effectiveness analysis will be performed from the societal perspective according to the intention-to-treat approach, with missing data imputed using multiple imputations [73]. CIs (95%) will be obtained by bias corrected and accelerated bootstrapping. The incremental cost effectiveness ratios will be calculated by dividing the differences in mean total costs between both groups by the difference in mean effects between both groups (eg, ZBI score of caregivers and BPRS and GAF scores of people living with schizophrenia). The incremental cost utility ratio will be calculated by dividing the incremental costs by the difference in the quality-adjusted life years assessed with the EuroQoL five-dimensional instrument (EQ-5D) between both treatment groups. These ratios will be graphically presented in a cost-effectiveness plane [74].

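### The cost-utility ratio rests on EQ-5D QALYs, but the EQ-5D is in no outcome list and in no row of the assessment table said to cover every instrument

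*Protocol article*

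**What the plan says.** The Cost-Effectiveness Analyses section of the protocol article plans two kinds of ratio. The first divides the cost difference by a difference in mean effects, with the ZBI of caregivers and the BPRS and GAF of people with schizophrenia as examples. The second is an incremental cost-utility ratio, whose denominator is the "difference in the quality-adjusted life years assessed with the EuroQoL five-dimensional instrument (EQ-5D) between both treatment groups".

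The measures themselves are set out in two places. Effect Measures lists the outcomes for each group. The caregiver list opens with "For family caregivers, the outcomes will include knowledge and skills about caregiving" and contains no quality-of-life or utility scale. For people with schizophrenia the only quality-of-life measure is "self-reported quality of life (World Health Organization Quality of Life Brief Scale"). Table 3 then gives the visit schedule, and Data Collection and Management describes its scope: "Table 3 provides an overview of all outcome measures and assessment instruments that will be used in this trial". Its quality-of-life row reads "Quality of life (World Health Organization Quality of Life Brief Scale"). No row names the EQ-5D.

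**The concern.** A cost-utility ratio needs a utility for each person at each time point, from which QALYs are built. The instrument named to supply those utilities is missing from the schedule that the assessment team would follow. This is more than a detail that a journal article leaves to the full protocol, because the article prints a row-by-row, visit-by-visit schedule and says that it covers all instruments. An analysis that depends on an instrument outside that schedule contradicts it.

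At stake is one of the planned economic ratios. Utilities not asked for at a visit cannot be collected later, so a gap noticed only at the analysis stage could not be repaired.

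**Working it through.** No figure in the plan has to be reproduced. The check compares the instrument that the analysis needs with every place where the article says what is measured.

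**What the analysis needs.** Cost-utility ratio = (difference in mean total cost) / (difference in mean QALYs). By the Cost-Effectiveness Analyses section, the QALYs come from the EQ-5D.

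**Where the EQ-5D could be scheduled:**

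| Place in the protocol article | Content | EQ-5D named? |
|---|---|---|
| Effect Measures, caregivers | 10 outcomes | No |
| Effect Measures, people with schizophrenia | 7 outcomes | No |
| Cost Measures | intervention, health care use, lost productivity | No |
| Process Measures | fidelity, quality, attitudes | No |
| Data Collection and Management (text) | timing, survey platform, reimbursement | No |
| Table 3 | 10 caregiver + 7 patient + 3 confounder + 3 cost + 3 process = 26 rows | No (0 of 26) |

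Outside the Cost-Effectiveness Analyses section, the EQ-5D appears only in the list of abbreviations.

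**Consequence for the schedule.** Table 3 has five assessments (months 1-2, 3-4, 5-6, 7-8 and 9-10). Utilities are scheduled at 0 of these 5, so the denominator has no data source.

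**Could something else in the plan supply the denominator?**
- The WHO brief quality-of-life scale is scheduled at all five assessments, but only for people with schizophrenia. It is not the instrument named for QALYs, and no mapping to utilities is described.
- Caregivers have no quality-of-life scale at all.
- Multiple imputation is planned for missing data in the economic analysis. It fills gaps in a variable that was measured in some participants, and it cannot create one measured in nobody.

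**What is not affected.** The ZBI, BPRS and GAF each have a row in Table 3 with all five assessments marked, so the ratios built on them have their denominators. The three cost components also have rows, so the comparison of total costs stands.

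**A related ambiguity.** The Cost-Effectiveness Analyses section does not say whose QALYs count. Costs are taken from a societal perspective and cover both people with schizophrenia and caregivers, so the respondent cannot be inferred from the cost side.

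**The case against.** The strongest reply is that naming the EQ-5D as the source of the QALYs is itself a statement that it will be used, and that Effect Measures introduces its lists with wording that is not closed. On that reading a row was simply left out of Table 3. This is possible, and the document does not settle it. A reader might infer that the trial will not collect utilities and that the ratio is lost whatever happens, and the text does not support that. What stands is the contradiction: Table 3 claims to be complete, and the assessment team would work from it.

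A second reply is that little depends on this ratio. The abstract mentions only incremental cost-effectiveness ratios, and none of the three stated aims mentions QALYs or cost-utility. This holds and limits the weight of the point. A reader might conclude that the economic evaluation as a whole, or half of it, fails. It does not, because several ratios and the cost comparison have scheduled data.

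Two further inferences are tempting and should not be drawn:
- **That caregivers' production losses will be understated.** Cost Measures says that "costs include absenteeism due to sick leave, which will be assessed by monthly sick leave calendars", which could suggest that leave taken for caregiving goes unrecorded. That judges the calendar by its name. The form is not shown, and the same section's valuation rule covers losses from caregiving as well as sickness and provides a value for people without a job.
- **That the number of missing utility values can be counted as families times visits.** The plan allows for 20% attrition, utilities belong to persons rather than families, and a family may take part with only one member. Only the count of 0 out of 5 scheduled assessments is supported.

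Finally, the loss is avoidable. The article expects recruitment and the program to start in September 2020 and collects questionnaires online, so correction before the first assessment was feasible on its own dates.

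**Conclusion.** The point holds as an internal contradiction between the analysis section and the measurement schedule. If Table 3 is followed as written, 0 of 5 assessments collect utilities and the cost-utility ratio cannot be calculated. This conclusion assumes that Table 3 is as complete as the article says and that no utility mapping is planned elsewhere. If the EQ-5D was always intended, the ratio is safe but the outcome list and Table 3 still need correcting.

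The effect is confined to one economic ratio. The effectiveness analysis, the ZBI, BPRS and GAF ratios, the total cost comparison and the process evaluation are untouched. It should be fixed, and before data collection because missed utilities cannot be recovered, but it is not a fault that undermines the trial.

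**What to change.** Before the first assessment in months 1-2, do one of the following:

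1. Add the EQ-5D to Effect Measures and to Table 3 at all five assessments, and state whether people with schizophrenia, caregivers or both complete it. Say in the Cost-Effectiveness Analyses section whose QALYs form the denominator.
2. Delete the cost-utility ratio from the Cost-Effectiveness Analyses section and keep the ratios whose measures are scheduled.

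The first option adds a few items to an online survey that already takes about 20 minutes for people with schizophrenia and 45 minutes for caregivers. The second is an edit to the text and gives up the QALY result. Either is a change to outcomes or analyses, which the Ethical Consideration section already commits the team to report.

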### Data Monitoring and Evaluation

In order to ensure the smooth progress of the intervention and protect participants’ welfare, a data monitoring committee (DMC) will be established. The DMC will involve administrative staff from both the hospital and its 12 affiliated community health centers, who are independent from the sponsor and have no competing interests. The main responsibility is to monitor the study progress and deal with any adverse event during the study process, which will be reported by the medical team to the principal investigator (YY) and then to the DMC. Every month, the DMC will hold a study meeting to summarize study progress, troubleshoot problems, and deal with any adverse events during the study. The DMC also has the right to terminate the intervention when it deems that the intervention is a large risk to participants.

### Ethical Consideration

The study protocol was reviewed and approved by the Institutional Review Board (IRB) of Xiangya School of Public Health Central South University (approval number: XYGW-2019-029). All procedures are in accordance with the Declaration of Helsinki. The WIFI program has been registered as a clinical trial (NCT04393896). Any modifications (eg, changes to eligibility criteria, outcomes, and analyses) to the study protocol will be reported to relevant parties (eg, investigators, IRB, trial participants, trial registries, journals, and regulators) immediately. The medical team will approach participants to fully inform them of the study aims and contents and acquire written informed consent from them before recruitment. The medical team will recommend the WIFI program to all people living with schizophrenia and their family members who come for free medicines, without any biased selection based on personal preference. Participation or refusal will not affect medicine acquisition and subsequent medical or nursing care. In order to protect participant confidentiality, personal information of participants will be collected only once during baseline data collection and then deidentified with newly generated numbers (instead of name, age, etc) after the trial. The deidentified data will only be shared or reported aggregately instead of individually. All data will be securely and secretly stored on a disk and managed by a special data specialist. Only the principal investigator and the research team will have access to the final trail data sets.

### Knowledge Dissemination

Trial results will be communicated to participants, health care professionals, the public, and other relevant groups through papers published in peer-reviewed journals (four to six international and two to four national), a PhD thesis, a master’s thesis, presentation at one national and one international conference, lectures targeted at people living with schizophrenia and family members in psychiatric hospitals, posters and pamphlets in community health centers, and popular science articles on WOA. Authorship will follow the ICMJE recommendation for authorship based on the criteria of substantial contributions to the conception or design of the work; acquisition, analysis, or interpretation of data for the work; drafting the work or revising it critically for important intellectual content; and final approval of the version to be published. The full protocol, participant-level data set, and statistical code are available from the first author (YY) and corresponding author ([name]) on reasonable request.

## Results

The study was funded in August 2018 and was approved by the IRB on January 15, 2019. Preliminary baseline data collection was conducted in May 2019 and completed in September 2019. The WIFI program is expected to start in September 2020.

## Discussion

Using a SWCRT design, the proposed study will develop a WIFI program fully aligned with the Reward Policy and test its effectiveness. Expected results will include the following: (1) significant improvement in outcomes for both people living with schizophrenia and their family members owing to WIFI program participation; (2) stronger impact for WIFI combined with the Reward Policy than the Reward Policy alone; and (3) development of a cost-effective replicable family management model for schizophrenia that can be integrated into the current national Reward Policy.

The study has some unique advantages and innovations. First, the WIFI program recruits the whole family of people living with schizophrenia as the intervention target, which may produce more far-reaching positive effects than interventions targeted at people living with schizophrenia alone or caregivers alone. In Asian countries like China, family cohesion and harmony are the core of the family-oriented culture. Interventions targeted at the family not only directly improve the well-being of each member, but also improve the family dynamic, which, in turn, will promote each member’s well-being. Second, the WIFI program is based on the most widely used social media platform in China (WeChat), which is accessible, affordable, feasible, and cost-effective. Compared with traditional on-site interventions, the WeChat-based intervention provides both synchronous and asynchronous communication that can serve a broad range of respondents who would otherwise not be recruited owing to time restraints and geographical constraints. Third, the WIFI program provides the most comprehensive intervention by integrating all three key components of family intervention that have been internationally recognized (psychoeducation, peer support, and private/professional support). Each component has its unique effect in improving the health outcome of people living with schizophrenia and their family members, and the components compensate each other to maximize the benefits to the family. Fourth, the stepped-wedge design has ethical advantages by ensuring all participants receive the intervention, as well as statistical advantages by generating more sound and robust scientific evidence than a traditional randomized cluster trial. Fifth, the WIFI program involves a medical team with both clinical psychiatrists and psychiatric nurses who work as both intervention implementers and data collectors. The medical team has a long close relationship with the community and is well accepted by people living with schizophrenia and their families, which can greatly increase the participant recruitment rate. In addition, the medical team knows about each person living with schizophrenia and can make more accurate assessments regarding the symptoms and functions of people living with schizophrenia, which can further increase the reliability and validity of the WIFI program.

One concern about this study is the potential attrition of participating people living with schizophrenia and their family members, which is very common in longitudinal intervention studies, especially those involving online interventions. Since all participants are recruited through the monthly medicine delivery process of the “686 Program” that has been running successfully for many years and the people living with schizophrenia are known to the medical team, we believe this stable and long-term community connection will increase program retention and reduce study attrition. Moreover, the use of the most widely accepted social media platform in China, WeChat, which is embedded in many aspects of daily life, is likely to reduce program and study attrition. Nevertheless, we account for attrition by estimating a 20% attrition rate in our study sample. In addition, the reimbursements for participants will increase by 25% for each successive assessment through the conclusion of the study to reflect participants’ ongoing commitment.

Another concern is the potential risk of privacy violation with the use of the WeChat platform as a means to deliver the intervention, especially the peer-support group through the WeChat group chat. It is likely that some personal information and chat records of participants may be disclosed intentionally or unintentionally by other participants. For each peer-support WeChat group, we will appoint a research team member to monitor participant interactions and flag privacy issues that emerge for group members. Regarding information and data collected through WeChat, we will store the data in an encrypted file managed by a member of the research team.

In conclusion, this innovative study will contribute to the development of a more cost-effective and evidence-based family management model in the community for people living with schizophrenia. The proposed study is among the first to develop and test a WeChat-based mHealth intervention to support family caregiving for schizophrenia in China. If found to be effective, the intervention could potentially be integrated into the current national policy to support family caregiving. The intervention could also be adapted for use in other populations having a persistent and disabling condition.

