## Methods

### Setting

The study will be conducted at Changsha Psychiatric Hospital (also named The Ninth Hospital of Changsha). Established in 1952 and affiliated to Changsha Civil Affairs Bureau, Changsha Psychiatric Hospital has the responsibility of prevention, treatment, and rehabilitation for all residents with mental illnesses in Changsha City. The hospital not only provides out-patient and in-patient health care, but also extends its services to community-based mental health care for its 12 affiliated communities, including the “686 Program” and Reward Policy implementation. The “686 Program” is China’s largest demonstration project in mental health service aimed at integrating hospital and community services for serious mental illnesses, with the following services provided mainly through community health workers: patient registration and initial assessment, free medication and regular follow-up in the community, management of community emergencies, and free emergency hospitalization [45-47]. In Changsha Psychiatric Hospital, a medical team involving three psychiatrists and four nurses is responsible for the “686 Program,” and the members circulate around the 12 communities each month to delivery free medicines to over 1000 registered clients who they know very well after long-term visits. The Reward Policy is a newly issued policy to encourage family care of people with serious mental illness, with RMB 200 (US $28.6) per month currently offered to each family registered under the 686 Program by Changsha Psychiatric Hospital.

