### Participants and Recruitment

Recruitment is estimated to start in September 2020. The study aims at recruiting 240 families of people living with schizophrenia from 12 communities affiliated to Changsha Psychiatric Hospital through the “686 Program.” Within each community, 20 eligible people living with schizophrenia will be randomly selected from the registry name list by a statistician, leading to a sampling frame of 240 families of people living with schizophrenia. Each family will be approached and invited to participate in the study during the monthly medicine delivery by the medical team from Changsha Psychiatric Hospital. We do not require both a person living with schizophrenia and a family caregiver to be recruited into the study at the same time. The entire family may benefit from the intervention as long as there is one member from the family participating*.* The medical team has been providing mental health services, including free antipsychotic medicine delivery, in the communities for a long time and thus knows very well about each family having a person living with schizophrenia, which greatly facilitates participant recruitment and retention. Detailed information about the research will be provided both orally and in written format to interested families by the medical team. All families will be fully informed of the study risks and benefits, and their right to drop out of the study at any time (Multimedia Appendix 3). Families agreeing to participate in the study will be invited to scan a WeChat barcode of the research program, so that they can be allocated to receive the intervention in the future. Our research team will include three psychiatrists who will complete clinical assessments of symptoms and functioning of the people living with schizophrenia through WeChat video chat. In addition, 10 postgraduate students will assist people living with schizophrenia and their caregivers to complete online questionnaires through WeChat. The research team will receive extensive training for both the intervention and evaluation to ensure quality and consistency.

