### Blinding

People living with schizophrenia, family caregivers, medical team members, and researchers cannot be blinded to the allocated treatment. The program team conducting the intervention will not be involved in assessing any of the outcomes. The data analyses by researchers will be blinded.

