### Intervention

Participants in the control group will receive the usual financial benefits of the Reward Policy and receive payments from Changsha Psychiatric Hospital. However, they will not have access to the WIFI program since they cannot scan the WeChat barcode for the research.

Participants in the intervention group will receive the usual financial benefits of the Reward Policy as well as the WIFI program that will include the following three key components: psychoeducation through WOA publications, peer-support through a WeChat chat group, and professional support through WeChat private chat and video calls (Table 2).

**Table 2 table2:** Content of the WeChat-based integrative family intervention program.

Component	Format	Frequency	Leader	Possible content/topics
Psychoeducation	WeChat official account publications	Weekly	Psychiatrists and researchers	What is schizophrenia? What causes schizophrenia? How is schizophrenia treated? What can be done to promote recovery in schizophrenia? What are the early signs of relapse? What support do families need? How can feelings of stigma be addressed?
Peer support	WeChat chat group of people living with schizophrenia	Daily	People living with schizophrenia volunteers	Introduce self and tell your story; identify a specific problem encountered to discuss with the group; discuss skills and techniques used to cope with challenging situations; share feelings and resources; organize offline activities for support and stress reduction, such as hiking, dinner, and group meetings.
Peer support	WeChat chat group of caregivers	Daily	Caregiver volunteers	Introduce self and tell your story; identify a specific problem encountered to discuss with the group; discuss skills and techniques used to cope with challenging situations; share feelings and resources; organize offline activities for support and stress reduction, such as hiking, dinner, and group meetings.
Professional support	Private WeChat chat and video call	Monthly	Psychiatrists	Evaluate symptoms and function in people living with schizophrenia; update on medication and treatment; troubleshoot specific problems; provide consultation, guidance, assistance, etc.

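### The plan contradicts itself on whether the staff who deliver WIFI also assess outcomes, which leaves the unblinded GAF and BPRS ratings without their only stated protection

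*Protocol article*

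**What the plan says.** Statements on who delivers and who assesses stand in six places in the protocol article.

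- **Blinding:** "The program team conducting the intervention will not be involved in assessing any of the outcomes". The same section says that "medical team members, and researchers cannot be blinded to the allocated treatment". Only the data analysis is to be blinded.
- **Discussion, fifth advantage:** the medical team consists of "clinical psychiatrists and psychiatric nurses who work as both intervention implementers and data collectors". It continues that "the medical team knows about each person living with schizophrenia and can make more accurate assessments regarding the symptoms and functions".
- **Effect Measures:** BPRS and GAF are the clinician-rated outcomes, "which will both be rated by psychiatrists".
- **Participants and Recruitment:** the research team includes "three psychiatrists who will complete clinical assessments of symptoms and functioning" by WeChat video. That research team is to be trained for intervention and evaluation alike.
- **Intervention, Table 2:** psychiatrists lead the monthly professional support by private WeChat chat and video call. Its content begins with "Evaluate symptoms and function in people living with schizophrenia".
- **Setting:** the hospital has "a medical team involving three psychiatrists and four nurses" for the 686 Program, and this team goes round all 12 communities each month.

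**The concern.** GAF and BPRS are judgement-based ratings. Once staff are acknowledged to be unblinded, keeping delivery and rating apart is the only protection the article states for them. The Discussion takes that protection away and presents the dual role as an advantage.

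A stepped-wedge trial is sensitive to this. Each community changes from control to WIFI on a known date. A rater who knows that date and scores more favourably afterwards produces a step in the data at the same point as the treatment indicator. The planned model, with cluster as a random effect and time as a fixed effect, cannot tell that step from a treatment effect. Blinding the analyst does not help, because the score has already been recorded.

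GAF is one of the two outcomes on which the sample size rests (Power Analyses). GAF and BPRS are both named as effect measures for the cost-effectiveness ratios (Cost-Effectiveness Analyses).

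**Working it through.** **Step 1. Set the statements side by side.**

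| Question | Blinding | Discussion | Other sections |
|---|---|---|---|
| Do those who deliver WIFI assess outcomes? | No, none | Yes: the medical team does both | Research team trained for both tasks (Participants and Recruitment) |
| Who rates symptoms and functioning? | Not the delivering team | The medical team | Psychiatrists (Effect Measures); three research-team psychiatrists (Participants and Recruitment) |
| Does delivery itself include such ratings? | Not addressed | Not addressed | Yes, monthly, led by psychiatrists (Table 2) |
| Are staff blinded? | No | Not addressed | Not addressed |

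The Discussion speaks of assessing symptoms and functions, so its data collection cannot be read as logistics alone. Those are the constructs of BPRS and GAF. The first row is a direct contradiction, and it does not depend on who the individual psychiatrists are.

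**Step 2. How a rating shift enters the estimate.** Suppose every rating made under WIFI is raised by b points and the true effect is θ. The shift is a constant multiple of the treatment indicator, so the estimate is centred on θ + b. The bias equals b.

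**Step 3. An illustration from the plan's own GAF inputs.** The plan states no bias figure, so there is nothing to reproduce.

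Inputs (Power Analyses): target change 52 − 42 = 10 points; α = 0.05, taken as two-sided because the article does not say; β = 0.15, so power is 85%.

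Implied standard error of the treatment effect:

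SE = 10 / (1.960 + 1.036) = 10 / 2.996 = 3.34 points.

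Chance of a significant result with θ = 0 and shift b: P(|Z + b/SE| > 1.96).

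| Assumed shift b (GAF points) | Declared significant |
|---|---|
| 0 | 5.0% |
| 1 | 6.0% |
| 2 | 9.2% |
| 3 | 14.7% |
| 5 | 32.2% |

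For b = 5: 5/3.34 = 1.50, and 1.96 − 1.50 = 0.46, which gives an upper-tail probability of about 0.32. The article gives no value for b, so every row after the first is an assumption.

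**Step 4. A second basis, to show how far the size depends on the model.** Take the usual stepped-wedge variance for new people in each period, with I = 12 communities, T = 5 periods, 20 × 0.8 = 16 evaluable per community, and ICC 0.05. The article states that ICC in the caregiver-burden calculation. In SD units, σ² = 0.95/16 = 0.0594 and τ² = 0.05. The design constants are U = 3(4+3+2+1) = 30, W = 0+9+36+81+144 = 270 and V = 3(16+9+4+1) = 90.

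Var = Iσ²(σ² + Tτ²) / [(IU − W)σ² + (U² + ITU − TW − IV)τ²] = 0.2204 / (5.344 + 13.5) = 0.0117.

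SE = 0.108 SD, and the difference detectable with 85% power is 0.108 × 2.996 = 0.324 SD. The article gives no GAF SD. An assumed SD of 15 makes this 4.9 points, and SDs of 10 to 20 make it 3.2 to 6.5.

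**The case against.** **The same people.** A reader might infer that the three psychiatrists of the medical team are the three who rate. The documents do not support this as fact. Setting places one group in the hospital's medical team, Participants and Recruitment places the other in the research team, and Table 2 says only that psychiatrists lead. An equal count is not identity. If the Blinding section governs, raters and deliverers are separate people, though the raters are still unblinded. This objection stands against the inference but not against the contradiction.

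**A bias large enough usually to be called an effect.** From Step 4 a reader might infer that a rater shift of about 4.9 points would usually be declared significant. That holds only with an assumed SD of 15, an ICC stated for caregiver burden, and new people in each period. The article follows the same families over five assessments. An assumed within-person correlation of 0.3 to 0.7 moves the detectable difference to about 0.28 to 0.19 SD, or 4.2 to 2.8 points at SD 15. On the plan's own GAF inputs (Step 3), a 4.9-point shift is declared significant only about 31% of the time. The objection therefore stands: the size depends on the model, and no calculation here measures an actual bias.

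**Full masking.** A reader might infer that a rater who is not told the sequence would be blind. Table 1 shows that every community is control at baseline and WIFI at step 4, so status is known in two of five periods. Families can disclose it, and the medical team visits all 12 communities. Masking can only be partial.

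**Scope.** Caregiver burden, the other sizing outcome, is collected by online questionnaire with help from postgraduate students, as are the other self-reported scales. Rehospitalization depends less on a rater's judgement and offers a partial cross-check. The point is confined to GAF and BPRS.

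**Conclusion.** The contradiction is certain: the Blinding section and the Discussion cannot both be carried out. Overlap between deliverers and raters of GAF and BPRS is likely, given the dual role in the Discussion, the joint training and the content of Table 2, but it is not stated. Detection bias is a risk, not a demonstrated fact, and its size is unknown.

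Any constant shift at crossover passes in full into the WIFI estimate. The illustrative false-positive rates, 9.2% for a 2-point shift and 32.2% for a 5-point shift, rest on a two-sided 5% level, no true effect, and the standard error implied by the plan's 10-point target at 85% power.

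This is not detail that a condensed article may leave to a fuller document, since the article makes two opposed statements. It should be settled before the first community crosses over, because every later rating is affected.

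**What to change.** 1. Reconcile Participants and Recruitment, Blinding, Intervention (Table 2) and Discussion so that the separation promised under Blinding holds for GAF and BPRS. State which psychiatrists rate and which deliver.
2. Have GAF and BPRS in each community rated by a psychiatrist who does not deliver professional support there and who, as far as possible, is not told its current step.
3. Keep the monthly evaluations made as part of professional support out of the outcome dataset.
4. In the Discussion, remove for these two outcomes the description of the medical team as collecting data and the claim that its familiarity with patients makes its assessments more accurate.
5. State as a limitation that raters cannot be fully masked, for the reasons given above.

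**Cost:** some re-rostering among psychiatrists, whose workload the article does not describe, and slightly noisier ratings because the rater knows the patient less well. The change mitigates the bias and does not remove it.
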